Randomization guarantees the avoidance of selection bias, excluding the preferential inclusion of patients in certain treatment arms. This approach, whilst not identifying which factors contribute to immunogenicity or which regimens are significantly better than others, will, however, highlight a treatment or treatment combination that warrants further investigation. The sample size per treatment must be large enough to ensure, with strong probability, that if one treatment or treatment combination is superior to all others by a specific amount, then it will have the largest sample mean and will therefore be selected. In particular, if one of the external immunostimulant conditions investigated shows higher clinical activity than that observed in the other conditions by a predetermined amount, that condition will be superior to the others with a given probability and will merit further clinical investigation. By enrolling six patients in each treatment arm, we will obtain a 90% probability of correctly selecting the best investigated external immunostimulant condition if the superior arm, if present, has a true expected outcome that is at least 15% higher in terms of irDCR (immune-related disease control rate) than that of the inferior arms [46]. Otherwise, the immunological primary endpoint (immunological efficacy) will guide the choice of treatment combination to further develop using the same method. If a treatment or a combination of treatments is not identified as superior, the vaccine regimen (without external immunostimulant conditions) will be considered for further investigation.

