#### Leukapheresis and vaccine manufacturing

At the end of the screening phase, patients will be randomized and will enter the leukapheresis and vaccine manufacturing phase. Each patient will be assigned to one of the following arms:

(1.) three daily doses of 8 Gy - 12 Gy radiotherapy delivered to one non-index metastatic field (optional to one additional field) between vaccine doses 1 and 2 and between doses 7 and 8, using IMRT-IMAT techniques;

(2.) daily 3 MU subcutaneous IFN-α for 7 days before leukapheresis;

(3.) both 1 and 2 external immunostimulant conditions;

(4.) neither 1 nor 2 external immunostimulant conditions.

At least six patients eligible for treatment will be enrolled per arm.

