### Sample size

This is a “randomized selection design” study based on the assumption that immunotherapy is expected to be effective only in patients showing efficient induction of antitumor immune responses (“targeted endpoint”) [49]. The Steinberg and Venzon approach permits the researcher to select one among a number of different treatment arms as being worthy of further evaluation in a subsequent study. This method requires an adequate gap in the number of immune responses among different arms be observed in order to limit the probability that the selected arm is, in actual fact, inferior to the others. Assuming an error probability of selecting an inferior arm of 10%, a gap of 2 patients with an immune response out of a total of 6 enrolled patients per arm is sufficient, regardless of the proportion of irOR expected in each arm, to show that the difference between the highest probability of response and the best response of the remaining arms is 15%. If the gap is inferior to 2 patients, no treatment arm can be considered better than another and new immunostimulating therapies will have to be identified to combine with the DC vaccine.

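### The 10% error of selecting an inferior arm holds for one use of the 2-of-6 gap rule; a second attempt on the immunologic endpoint can take it above 10%

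*Protocol article*

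**What the plan says.** The trial has four arms (RT, IFN-α, both, and "neither 1 nor 2 external immunostimulant conditions"), and "At least six patients eligible for treatment will be enrolled per arm".

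Two sections of the protocol article describe how an arm is chosen.

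- **Sample size** gives the rule and its error: "Assuming an error probability of selecting an inferior arm of 10%, a gap of 2 patients with an immune response" in six is held to be sufficient, "regardless of the proportion of irOR expected in each arm, to show that the difference between the highest probability of response" and that of the next best arm is 15%. If the lead is smaller than 2, no arm counts as better and new immunostimulating therapies are to be sought.
- **Trial design and statistical considerations** gives the complementary figure for irDCR: "we will obtain a 90% probability of correctly selecting the best investigated external immunostimulant condition if the superior arm, if present", is at least 15% better. It then continues: "Otherwise, the immunological primary endpoint (immunological efficacy) will guide the choice of treatment combination to further develop using the same method". If that also fails to identify a superior arm, the vaccine without added treatment is the regimen considered further.

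Neither section divides or adjusts the 10% for two attempts.

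**The concern.** An error probability worked out for one decision does not carry over to a procedure that decides again on a second endpoint when the first gives no answer. The second attempt brings its own chance of picking an inferior arm, and that chance adds to the first. The lead required on irDCR is seldom reached with six patients per arm, so the second attempt would be the usual course.

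The 10% and 90% figures justify six patients per arm and the choice of regimen for the next phase II or III trial. If the two-step rule is what is meant, a regimen could go forward at up to about twice the stated error.

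The Sample size section also says the lead is enough "to show that the difference between the highest probability of response and the best response of the remaining arms is 15" percent. A lead that often arises between identical arms does not show a difference of that size.

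**Working it through.** **Inputs from the protocol article.** Four arms of six; a lead of at least 2 over every other arm; a true advantage of 15 points; stated error 10%. Base rates are not fixed in the document, so they are varied. The historical figures in the section on dendritic cell vaccination (55.5% clinical benefit, about two-thirds immune response) serve as one assumed pair.

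**Assumptions.** The second attempt uses the same gap rule; it follows whenever no arm leads by 2 on irDCR; immune response is yes/no per patient; the endpoints are independent.

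**One endpoint.** With counts X_i ~ Binomial(6, p_i),

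P(select arm i) = Σ_{x=2..6} P(X_i = x) × Π_{j≠i} P(X_j ≤ x − 2).

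The error e is the sum of this over the three inferior arms, with true rates p + 0.15, p, p, p. Its maximum over p is 8.6% (p about 0.38); with only two arms it is 8.1%. A lead of 1 would give up to 31.9% with four arms. So 2 is the smallest lead that meets 10%, and the plan's figure reproduces for one endpoint.

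**Two attempts.** Let e1 be the error and n1 the probability of no selection on irDCR. Let e2 be the error on immune response if the same arm is 15 points better there, and q2 the probability that some arm is named when immune response is equal in all arms. Three of those four arms are inferior on irDCR.

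- Better on both endpoints: e1 + n1 × e2
- Better on irDCR only: e1 + n1 × 0.75 × q2

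At base rates of 40% on both endpoints:

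- both: 0.0856 + 0.7662 × 0.0856 = 0.151
- irDCR only: 0.0856 + 0.7662 × 0.75 × 0.1993 = 0.200

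At the historical rates (55.5% and two-thirds):

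- both: 0.0691 + 0.8049 × 0.0402 = 0.101
- irDCR only: 0.0691 + 0.8049 × 0.75 × 0.1316 = 0.149

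**Four equal arms.** With q1 and q2 the chances that some arm is named at each attempt, the overall chance is 1 − (1 − q1)(1 − q2). At 40%: 1 − 0.8007² = 0.359. At historical rates: 1 − 0.8230 × 0.8684 = 0.285. On irDCR alone the figures are 19.9% and 17.7%.

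| Base rate, both endpoints | 20% | 30% | 40% | 50% | 60% |
|---|---|---|---|---|---|
| Error, one endpoint | 6.6% | 8.2% | 8.6% | 7.8% | 5.9% |
| No selection on irDCR | 77.1% | 76.2% | 76.6% | 78.6% | 82.5% |
| Two attempts, better on both | 11.7% | 14.4% | 15.1% | 13.9% | 10.8% |
| Two attempts, better on irDCR only | 15.9% | 19.1% | 20.0% | 19.0% | 15.9% |
| Equal arms, winner named, two attempts | 29.6% | 34.5% | 35.9% | 34.4% | 29.8% |

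The maxima over all pairs of base rates are 15.1% (both) and 20.0% (irDCR only). At higher rates the error falls: at 70% on both endpoints it is 5.6% and 10.4%.

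**Correlation.** Simulation with a within-patient correlation of 0.9 at 50% base rates gives 13.1% (both), 17.8% (irDCR only) and 29.9% (equal arms). Positive correlation lowers the figures without restoring 10%.

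**The case against.** **The two-step gap rule is a joint reading of two sections.** The Trial design section mentions no gap; it speaks of the largest sample mean. The Sample size section stops when the lead is below 2. The Immunologic efficacy section analyses DTH as a 0–80 score with non-parametric tests, not as a yes/no response. This stands, so the reading must be stated as an assumption. If the Sample size section alone governs, the 10% is sound. If the Trial design section means selection without the 2-patient lead, the 10% does not hold either, since a lead of 1 gives up to 31.9%.

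**The size depends on the scenario.** A reader might infer that the error is 15–20% in general. The documents do not support that. At the historical rates, with the best arm ahead on both endpoints, it is 10.1%, essentially the stated value. The 40% base rate is not in the protocol. The 20% case assumes a benefit on irDCR with none on immune response, which fits poorly with the design premise that benefit requires an immune response. What remains is that the 10% is claimed for any response rate, so a case above it counts.

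**The equal-arms figures answer a different question.** A reader might set 28–36% beside the 10% and conclude that the bound is broken threefold. With equal arms none is inferior, and the plan claims no control of false winners. It disclaims identifying significantly better regimens, and under the secondary clinical objectives it admits many false positives. Those figures bear only on the claim that the lead shows a 15% difference.

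**Conclusion.** The point holds in a limited form. The 10% is right for one application of the gap rule to one endpoint. If the second attempt is the same rule on a yes/no immune response, and the endpoints are independent, the error is at most about 15% with the best arm 15 points ahead on both endpoints (10% at historical rates). It is at most about 20% with the best arm ahead on irDCR only (15% at historical rates). A bound stated for every response rate therefore fails under the plan's own second step, though not at every rate.

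Separately, a 2-patient lead does not show a 15% difference. Between four identical arms it names a winner in up to 20% of trials on one endpoint (18% at 55.5%) and up to 36% over two attempts (28.5% at historical rates).

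It might also be inferred that one of the two primary endpoints must become the sole basis for selection. The documents set both a clinical and an immunologic primary objective, so that is a design choice and not a correction.

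**What to change.** 1. Reconcile the Trial design and Sample size sections on what follows when no arm leads on irDCR: a second attempt on the immunologic endpoint, or a stop. They also differ on the final outcome (vaccine alone, or a search for new therapies), and the same edit should settle that.
2. If the second attempt stays, say how immune response is counted for selection. Replace the 10% with the error of the two-step rule: up to about 15%, or about 20% if the arms differ on irDCR only. Correct the matching 90% in the Trial design section in the same way. As one minus the error, that figure counts trials with no selection as correct, and the text should say so.
3. Delete the statement that the lead shows a 15% difference, and report the selected arm's difference with a confidence interval.

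This changes wording and two stated figures and needs no further patients. The downside is a less favourable stated error.

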### Primary objectives

#### Clinical objective

To select the regimen that has the best irDCR defined as the proportion of subjects with an immune-related best overall response (irBOR) of confirmed immune-related complete response (irCR), immune-related partial response (irPR) or immune-related stable disease (irSD). The irDCR will be compared in the different treatment arms to identify possible differences in clinical activity between the different external immunostimulant conditions combined with the autologous tumor lysate-loaded DC vaccine.

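### The design and sample-size sections give different selection rules for the same six patients per arm: the deciding endpoint, the winning criterion and the action when no arm wins all differ

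*Protocol article*

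**What the plan says.** **Trial design and statistical considerations.** Six patients per arm are justified by a true outcome "at least 15% higher in terms of irDCR (immune-related disease control rate) than that of the inferior arms". The section describes a superior treatment in these terms: "then it will have the largest sample mean and will therefore be selected". No minimum observed lead is given. The fallback reads: "Otherwise, the immunological primary endpoint (immunological efficacy) will guide the choice of treatment combination to further develop using the same method". If no treatment or combination is identified as superior, "the vaccine regimen (without external immunostimulant conditions) will be considered for further investigation".

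**Primary objectives, Clinical objective.** This agrees on the endpoint: "To select the regimen that has the best irDCR".

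**Sample size.** For the same six patients per arm and the same 15% difference, the rule is a lead of two patients with an immune response, with a 10% error probability of selecting an inferior arm. It is said to hold "regardless of the proportion of irOR expected in each arm". irDCR does not appear. If the lead is below two, "no treatment arm can be considered better than another and new immunostimulating therapies will have to be identified to combine with the DC vaccine".

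**Immunologic endpoint assessment.** DTH is reduced to a best normalized score on a 0–80 scale (any post-treatment test, ATL or KLH) and compared across arms by non-parametric tests. If that shows no difference, the ELISPOT fold increase is compared by t-test. In both cases the objective is met by statistical significance.

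**Secondary objectives.** irORR is listed here. The abbreviation irOR is not defined.

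**The concern.** Choosing a regimen is the trial's main decision, and three parts of that decision differ between the sections.

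- **Endpoint.** It is irDCR in one section and immune response in the other, with irOR in the same sentence. irDCR counts stable disease and an objective response rate does not, so they can rank four small arms differently.
- **Winning criterion.** One section takes the largest mean, the other needs a lead of two patients. A one-patient lead wins under the first and not under the second.
- **No winner.** One section considers vaccine alone, the other requires new stimulants to be found.

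There is also a mismatch in kind. A two-of-six lead needs each patient to be a responder or not, while the immunologic endpoint is defined and tested as a score or a ratio.

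At stake is whether the next step can be read from the protocol once the 24 results are in. The trial is open-label, so an unambiguous rule matters more than usual.

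**Working it through.** **Inputs.** Four arms; n = 6 per arm, a stated minimum ("At least six patients eligible for treatment will be enrolled per arm"), taken here as exactly six; true advantage d = 0.15; required lead 2. The documents give no base rate p for the arms, so p is an assumption. Two anchors come from the background text: 0.555 (PR + SD in the group's earlier studies) and 0.667 (about two-thirds of patients with an immune response).

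**Formulas.** The best arm has rate p + 0.15 and the other three have rate p. Let b and i be the binomial probabilities (n = 6) for the best arm and for an inferior arm, and B and I their cumulative sums. With x from 2 to 6:

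- P(correct) = Σ b(x) · I(x−2)³
- P(wrong) = 3 Σ i(x) · I(x−2)² · B(x−2)
- P(no lead) = 1 − P(correct) − P(wrong)

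**The plan's own figures.** Under the lead rule with four arms, P(wrong) never exceeds 8.6% for p from 0 to 0.85, so the 10% in the Sample size section holds as an upper bound. The 90% probability of correct selection in the design section does not reproduce. Taking the highest count with ties split at random gives 46% to 72% over the same range, and 47% at p = 0.555. That is a separate numerical matter; here it shows that the two criteria behave very differently.

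**Worked case, p = 0.555 (best arm 0.705).**

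- Correct: x = 3: 0.1799 × 0.0659³ = 0.0001; x = 4: 0.3225 × 0.2471³ = 0.0049; x = 5: 0.3083 × 0.5484³ = 0.0508; x = 6: 0.1228 × 0.8302³ = 0.0703. Sum 0.126.
- Wrong: x = 4: 3 × 0.2818 × 0.2471² × 0.0666 = 0.0034; x = 5: 3 × 0.1406 × 0.5484² × 0.2465 = 0.0313; x = 6: 3 × 0.0292 × 0.8302² × 0.5690 = 0.0344. Sum 0.069.
- No lead: 1 − 0.126 − 0.069 = 0.805.

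**Over base rates.**

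| p | correct | wrong | no lead |
|---|---|---|---|
| 0.05 | 0.189 | 0.017 | 0.794 |
| 0.2 | 0.163 | 0.066 | 0.771 |
| 0.3 | 0.157 | 0.082 | 0.762 |
| 0.4 | 0.148 | 0.086 | 0.766 |
| 0.555 | 0.126 | 0.069 | 0.805 |
| 0.667 | 0.094 | 0.040 | 0.866 |
| 0.8 | 0.030 | 0.003 | 0.967 |

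A single application of the lead rule therefore ends without a winner in 76–87% of trials for p from 0.05 to 0.667.

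**If the lead rule is applied twice** (irDCR, then immune response), and the two endpoints are treated as independent:

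- No lead on either: 0.805 × 0.866 = 0.70 at 0.555 then 0.667; 0.766 × 0.766 = 0.59 with both at 0.4. No winner is still the most likely result.
- Wrong selection, first-step wrong + first-step no lead × second-step wrong: 0.069 + 0.805 × 0.040 = 0.101 at 0.555 then 0.667; 0.040 + 0.866 × 0.040 = 0.075 with both at 0.667; 0.086 + 0.766 × 0.086 = 0.152 with both at 0.4.

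**The case against.** **The design section already gives an order.** It puts irDCR first and immunological efficacy second, by the same method, and the Sample size count of immune responses could be that method applied to the second endpoint. This is a fair reading, and it reduces the endpoint conflict to an ordered pair plus a stray irOR. It does not remove the conflict. The Sample size section states no order, never mentions irDCR, and presents the lead in immune responses as the basis for the same n and the same 15%. Nor does the design section mention a two-patient lead.

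**The responder cut-off may sit in the full protocol or SAP.** This stands as far as the missing cut-off goes: the article uses DTH-positive and DTH-negative as working categories, and a condensed text may leave the number elsewhere. What remains is what the article does state, namely a rule that counts responders beside an endpoint analysed as a score or ratio by significance tests. If the shared method is taken to mean the largest mean, arms can be ranked on mean score, but then the two-patient lead and its 10% error do not apply to that step.

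**A reader might infer that the two no-winner actions are opposite.** The text does not support that. Both keep the vaccine as the backbone, and vaccine alone could be considered while new partners are sought. They are different and unreconciled.

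**A reader might infer that two tries clearly breach the 10% error.** That is not shown. At the rates anchored in the documents the two-step figure is 10.1%, and it is 7.5% with both at 0.667. The 15% needs an assumed 0.4 on both endpoints. All of these figures assume independence, while the article reports that DTH response and clinical outcome are associated. If the two endpoints agreed in every patient, the second step would add nothing.

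**A reader might also set the chance of selecting some arm when all four are equal against the 10%.** That is a different quantity: with equal arms no arm is inferior, so no inferior arm can be selected.

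**Conclusion.** The point holds as an unreconciled contradiction in the trial's primary decision rule. The design and Sample size sections differ on the deciding endpoint, on the winning criterion and on what follows when no arm wins, and the counting rule does not fit the immunologic endpoint as the article defines and analyses it.

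The size rests on how often the disputed branch is reached. With four arms of exactly six, a true 15-point advantage for one arm and equal rates in the others, no arm leads by two in 76–87% of trials for base rates of 0.05 to 0.667, and in 97% at 0.8. The base rates are assumed. Under an ordered two-step rule the no-winner share falls but stays above half in the cases worked (59% and 70%, assuming independence).

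The conclusion does not depend on the two-step error figures, nor on any suggestion that the choice would in fact be made after seeing data. An SAP not shown here might settle the order, but the protocol text would still contradict itself.

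**What to change.** State one ordered rule and use it in the same words in both sections:

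1. Select on irDCR if one arm leads all others by at least two of six.
2. If none does, apply the same lead rule to a binary DTH responder derived from the endpoint already defined: the best post-treatment result, for ATL or KLH. The sponsor should choose and justify the cut-off before any data are seen. A responder restricted to one antigen or one time point would create a new conflict with that definition.
3. If there is still no lead, follow one stated action. The two present actions must be reconciled; which one to adopt, or whether to combine them, is for the sponsor.

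Remove irOR from the Sample size section, and replace the largest-mean description in the design section with the lead rule. Say how the significance tests on the DTH score and the ELISPOT ratio relate to selection. Quote correct, wrong and no-selection probabilities for the two-step rule over a range of base rates, allowing for correlation between the two endpoints.

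The cost is protocol wording and a short calculation. No extra patients, visits or assays are needed.

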### Primary objectives

#### Clinical objective

To select the regimen that has the best irDCR defined as the proportion of subjects with an immune-related best overall response (irBOR) of confirmed immune-related complete response (irCR), immune-related partial response (irPR) or immune-related stable disease (irSD). The irDCR will be compared in the different treatment arms to identify possible differences in clinical activity between the different external immunostimulant conditions combined with the autologous tumor lysate-loaded DC vaccine.

#### Immunologic objective

The immunologic efficacy of the different external immunostimulant conditions used in combination with the autologous tumor lysate-loaded DC vaccine will be assessed by DTH development against KLH and tumor homogenate and also by IFN-γ-ELISPOT analysis of circulating effectors specific for tumor antigens known to be expressed in melanoma, as described in the “Immunologic endpoint assessment” section.

### Secondary objectives

#### Clinical objectives

To define further the clinical efficacy of the different treatment arms, including an analysis of OS (as indicated by median survival and survival rates at 1- and 2-year follow-ups), immune-related time to progression (irTTP), immune-related overall response rate (irORR), immune-related duration of response (irDOR), immune-related time to response (irTTR) and immune-related progression-free survival (irPFS). All time-dependent clinical endpoints (irTTP, OS) will be estimated using the Kaplan-Meier method and the log rank test will be performed on differences in these endpoints across the treatment arms. Frequency tables will be created for all categorical variables. Continuous variables will be presented using mean and standard deviation or median and range. Given the explorative intent of the study and the limited sample size, we are aware that we may be exposed to a high level of false positive results. Unless otherwise indicated, the analysis of demography and baseline characteristics will be performed on all randomized patients. Demographic and laboratory results will be summarized using descriptive statistics.

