## Background and rationale

### Malignant melanoma

Malignant melanoma represents one of the most challenging problems in modern oncology. Although it accounts for only 4% of incident cases of skin cancers, it is responsible for more than 80% of all skin cancer deaths [1]. Moreover, its incidence has dramatically increased in recent decades [2]. Whilst early stage melanoma (i.e. primary thin melanomas without regional lymph node or distance involvement) has a very favourable prognosis with a recurrence rate of less than 10% at five years, patients with advanced disease experience a very poor clinical course, with median survival ranging from 4 to 12 months [3]. Furthermore, until very recently, the clinical efficacy of the available treatments was disappointing. In early 2011, the FDA approved the clinical use of ipilimumab, a CTLA 4-blocking monoclonal antibody which, in addition to significantly improving the survival of patients with metastatic melanoma, primarily demonstrated the effectiveness of anti-cancer therapy based only upon immune system targeting [4,5]. However, ipilimumab causes a generalized activation of the immune system which can, in extreme cases, induce severe autoimmune side-effects [6]. On this basis, immunotherapeutic approaches capable of eliciting effective anti-tumor immune responses without the related autoimmunity must be sought developed.

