Like de Vries et al. [17], we saw that patients who developed anti-tumor immunity after vaccination experienced a better clinical outcome [16,18]. In particular, we observed that patients developing delayed type hypersensitivity (DTH) against autologous tumor lysate or keyhole lympet hemocyanin (KLH) after at least four courses of the vaccine showed a median overall survival (OS) of 22.9 months compared to the 4.8 months of DTH-negative cases (Log-rank test, p = 0.007) [16]. Intriguingly, both the disease control rate (DCR) and OS obtained with DC vaccination considerably exceeded those obtained with ipilimumab in a similar patient setting [4]. However, although differentiation and maturation conditions used for the production of DC vaccines have been standardized, only two-thirds of patients develop potentially effective anti-tumor immune responses. We recently reported that patients showing upregulated expression of tumor endothelial marker-8 (TEM-8) in monocyte-derived DC upon maturation do not develop immune reactivity against autologous tumor lysate (ATL) or KLH on DTH and experience a very poor clinical outcome after DC vaccination [19].

TEM-8 is an integrin-like cell surface protein specifically expressed by embryonic and tumor endothelial cells (not, however, in the adult endothelium) whose functions are still not fully understood [20]. It was recently shown that TEM-8 is upregulated in tumor-associated endothelial cells after exposure to interleukin-1β (IL-1β) [21]; interestingly, IL-1β, together with tumor necrosis factor-α (TNF-α) and other cytokines produced by tumor cells (melanoma included) [22], can negatively affect the differentiation of monocyte-derived DC in vitro [23]. As IL-1β and TNF-α are components of the cytokine maturation cocktail currently used to prepare the DC vaccine, it would not be surprising that, at least in a subset of patients, these cytokines support the differentiation of DC toward an immunosuppressive TEM-8 + phenotype rather than the more immunogenic and clinically active phenotype. In light of this, new treatment conditions capable of preventing such an occurrence should be identified.

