#### ELISPOT analysis

IFN-γ-ELISPOT assay will be performed using a commercial kit (Tema Ricerca, Bologna, Italy) according to the manufacturer’s instructions. Total PBMCs (10^5^ cells/well) will be used as responding cells and stimulated with 1 μg/mL of peptide covering the entire set of tumor antigens known to be expressed in melanoma (tyrosinase, MART1, MAGEA3, MAGEA1, gp100, NY-ESO, SOX2 and survivin; JPT GmbH, Germany). Plates will be evaluated by a computer-assisted ELISPOT reader (Eli.Expert, A.EL.VIS, Hannover, Germany). The patients’ DTH scores will also be evaluated in combination with IFN-γ-ELISPOT analysis of tumor antigen-specific circulating effectors in the different treatment arms with the same time schedule. In particular, if no significant difference across the treatment arms is found for DTH testing, the distribution of the fold increase (*i.e*. the post-vaccine: pre-vaccine ratio values) in Spot Forming Cells (SFC)/100,000 total PBMC recorded after at least four vaccine doses compared to pre-vaccine values, obtained by ELISPOT analysis and after subtraction of SFC observed in non-stimulated PBMC, will be evaluated using the Student’s t-test across the different treatment arms. If differences are found to be statistically significant (significance level 0.05), the specific primary objective will be considered fulfilled.

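### Referred to chi-square, the four-arm log-rank test with about six patients per arm understates p-values, clearly for mature overall survival and mildly for irTTP; a permutation p-value corrects this

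*Protocol article*

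**What the plan says.** Under the clinical part of the secondary objectives, the article plans Kaplan-Meier estimates for irTTP and OS and adds that "the log rank test will be performed on differences in these endpoints across the treatment arms". It gives no reference distribution, significance level or expected number of events for this test. The only explicit level, "significance level 0.05", belongs to the ELISPOT comparison.

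The section on leukapheresis and vaccine manufacturing sets the size: "At least six patients eligible for treatment will be enrolled per arm". The selection argument under trial design also rests on six per arm ("By enrolling six patients in each treatment arm"). OS is to be summarised by its median and by "survival rates at 1- and 2-year follow-ups". The same paragraph as the log-rank plan concedes that, with an exploratory aim and few patients, false positives may be frequent. It gives no figure and no remedy.

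**The concern.** The four-sample log-rank statistic follows chi-square with 3 degrees of freedom only in large samples. With 24 patients in four groups its upper tail is heavier, so the usual 5% critical value is exceeded too often even when the arms do not differ. Each printed p-value is then too small before any multiplicity is counted. That is a different matter from running many tests in a small trial, which is how most readers would take the article's caveat.

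At stake is the reading of the survival comparison. A nominally significant OS difference among these arms would look stronger than it is.

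**Working it through.** **The plan's own figure.** There is none for this test. The 10% error in the sample-size section belongs to the rule requiring a gap of two responders among six. Exact enumeration of that rule with four arms and a 15% difference gives a maximum error of 8.6%. That rule does not involve the log-rank test.

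**Inputs from the article.**
- Four arms, six patients each (the stated minimum; equal allocation assumed).
- OS in advanced disease: "median survival ranging from 4 to 12 months".
- The group's own earlier data: "median overall survival (OS) of 22.9 months compared to the 4.8 months of DTH-negative cases", and "only two-thirds of patients develop potentially effective anti-tumor immune responses". These give a mixture of 2/3 with median 22.9 months and 1/3 with median 4.8 months.
- OS horizon: one and two years.

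**Assumptions.** Chi-square reference, 5% level, exponential survival, the same censoring in every arm. Accrual is not given, so follow-up is varied.

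**Statistic.** At each event time j, with d_j events among n_j at risk and n_kj at risk in arm k:
- O_k − E_k = Σ_j (d_kj − d_j·n_kj/n_j)
- V_kl = Σ_j [d_j(n_j − d_j)/(n_j − 1)]·(n_kj/n_j)·(δ_kl − n_lj/n_j)
- X² = (O − E)′V⁻(O − E), rejected if X² > 7.815 (chi-square, 3 df, 5%).

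The code agreed with a standard package on five test data sets.

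**Expected deaths.** With a common cut-off at F months and median m, deaths = 24·(1 − 2^(−F/m)). For m = 12 and F = 24: 24·(1 − 0.25) = 18.0. For m = 22.9 and F = 12: 24·(1 − 0.695) = 7.3. For the mixture at F = 24: (2/3)·12.4 + (1/3)·23.2 = 16.0.

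**False-positive rate, four identical arms of six, 40,000 trials per row** (simulation standard error about 0.15 points: √(0.1·0.9/40,000) = 0.0015). U(a–b) means censoring uniform between a and b months.

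| Median OS (months) | Follow-up (months) | Mean deaths of 24 | Rate at nominal 5% |
|---|---|---|---|
| 4.8, 12, 22.9 or mixture | all deaths seen | 24.0 | 10.0–10.3% |
| 4.8 | cut at 24 | 23.2 | 10.2% |
| 4.8 | cut at 12 | 19.8 | 9.4% |
| 12 | U(24–48) | 20.7 | 9.5% |
| 12 | cut at 24 | 18.0 | 8.9% |
| 12 | U(12–36) | 17.5 | 8.6% |
| mixture | U(24–48) | 18.4 | 8.8% |
| mixture | cut at 24 | 16.0 | 8.4% |
| mixture | U(12–36) | 15.7 | 7.8% |
| 22.9 | U(24–48) | 15.7 | 8.3% |
| 22.9 | cut at 24 | 12.4 | 7.3% |
| 22.9 | U(12–36) | 12.1 | 7.0% |
| 12 | cut at 12 | 12.0 | 7.0% |
| 22.9 | cut at 12 | 7.3 | 5.6% |

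Further runs with other random numbers agreed to within about half a percentage point. The boundary between mature and immature is not sharp: with a 12-month median and censoring uniform over 0–24 months, 11.0 deaths gave 7.7%.

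**Nominal 1%.** The rate was 3.2% with all deaths seen, 2.7–2.9% for a 12-month median with 17.5 to 20.7 deaths, and 2.3% with about 15 deaths.

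**irTTP.** With progression times rounded up to the 12-weekly scans through week 48, the rate was 6.1–7.2% over the medians tried.

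**Cause.** Without censoring, the rate falls from about 10% at six per arm to 9.7% at seven, 8.1% at ten and 6.8% at twenty. The simulated 95th percentile of X² at six per arm is 9.96 instead of 7.815. This is a small-sample failure of the reference distribution.

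**After the fix.** A permutation log-rank test (399 relabellings, 6,000 trials) rejected in 5.3% of trials with no censoring and 4.7% with U(12–36); the standard error is √(0.05·0.95/6,000) = 0.28 points. With strongly unequal censoring between arms it gave 4.2%, against 7.3% for chi-square.

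**Power.** One arm's median multiplied by 2, 3 or 4.77 (22.9/4.8), no censoring:
- chi-square, uncorrected: 24%, 41%, 65%
- permutation, same simulated trials: 14%, 26%, 47%
- chi-square recalibrated to a true 5%: 13%, 27%, 50%

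The raw rejection rate drops by up to 65 − 47 = 18 points. Against a correctly calibrated test there is essentially no loss.

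**The case against.** The strongest reply is that the article never says chi-square. A permutation log-rank test is still a log-rank test, and the way its p-value is obtained could be set in a full protocol or analysis plan that is not shown. The article also admits to a risk of false positives and names small sample size as a reason. No decision hangs on the test: regimen selection uses irDCR or, failing that, the immunological endpoint, and the success rules tied to significance concern DTH, ELISPOT, DC yield, potency and TEM-8.

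Much of this stands. It makes the finding conditional on the default reference and limits its consequence. It does not remove the point, because the named test run in its usual form gives understated p-values, and a warning without a figure does not let a reader correct them.

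A reader might infer more than the article supports:
- **That every survival p-value is understated by nearly half.** Inflation of that order needs mature OS. It is smaller with few deaths, mild for irTTP, and shrinks if arms exceed the minimum of six.
- **That the choice of regimen is compromised.** No selection rule uses OS or irTTP.
- **That the remedy costs nothing, or is exact through randomisation alone.** Nominally significant results become rarer, and exactness also needs censoring that does not depend on arm.

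**Conclusion.** The point holds, conditionally and with limited reach. If the usual 3-df chi-square reference is used with about six patients per arm, the false-positive rate at nominal 5% is about 8-10% for mature OS (about 15 or more deaths), about 5-7% for immature OS (about 7-12 deaths) and about 6-7% for irTTP. At nominal 1% it is about 2-3% for mature OS.

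The chi-square reference, the 5% level and the follow-up patterns are assumptions; the OS medians and the responder share are the article's own. With every death observed the rate does not depend on the shape of the survival curve, because the test then uses ranks only. The consequence is confined to the interpretation of secondary, exploratory survival p-values.

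**What to change.** In the clinical secondary objectives, add a sentence to this effect: *P-values for the log-rank comparisons of OS and irTTP across the four arms will come from a permutation (re-randomisation) log-rank test with at least 10,000 re-allocations of treatment labels under the trial's randomisation scheme; the test is exact when censoring does not depend on arm.*

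With 10,000 re-allocations the Monte Carlo standard error at p = 0.05 is √(0.05·0.95/10,000) = 0.002, small enough for reporting.

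The cost is slightly more analysis code and less favourable p-values. No extra patients or data are needed.
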